# A personalized follow-up of kidney transplant recipients using video conferencing based on a 1-year scoring system predictive of long term graft failure (TELEGRAFT study): protocol for a randomized controlled trial

**DOI:** 10.1186/1471-2369-16-6

**Published:** 2015-01-28

**Keywords:** Kidney transplantation, Personalized follow-up, Video conferencing, Randomized clinical trial

## Abstract

**Background:**

Numerous well-established clinical parameters are taken into consideration for the follow-up adaptation of kidney transplant recipients, but there are important disparities between countries, centres and clinicians. Therefore, novel scoring systems have been developed, for instance the Kidney Transplant Failure Score (KTFS) which aims to stratify patients according to their risk of return to dialysis. We hypothesize that the efficiency of the follow-up after one year post-transplantation can be improved by adapting it to the risk of graft failure defined by the KTFS estimation.

**Methods/design:**

We propose a phase IV, open label, randomized, multicentric and prospective study. The study is registered with the Clinical Trials Registry NCT01615900. 250 patients will be allocated to one of two arms: the eHealth program versus the standard of care at hospital. In the standard group, patients classified at low-risk (KTFS ≤ 4.17) will be scheduled 4 visits at hospital per year, whilst high-risk patients will visit hospital 6 times. In the eHealth group, patients classified at low-risk will be interviewed 3 times by video conferencing and once at hospital, whilst 6 visits at hospital and 6 video conferencing will be scheduled for high-risk patients.

**Discussion:**

The current study allows to scientifically evaluate the etiologic impact of a novel eHealth program. This is important to clarify the possible contribution of telemedicine in the improvement of medical follow-up. The proposed design based on 4 different sub-groups can be interesting to evaluate other personalized medicine programs.

## Background

The prevalence of renal insufficiency is increasing in all developed countries, mainly due to the ageing population, and is leading to an increased prevalence of end stage renal disease (ESRD). In France, the prevalence of ESRD was estimated to be 70,700 cases, with 56% of patients under dialysis and 44% with a functional transplant [1]. Compared to renal transplantation, extra renal dialysis is associated with higher mortality [2] and lower quality of life [3, 4]. Additionally, the overall long-term cost of transplantation is lower than that of dialysis. In France in 2007, the mean annual cost of hemodialysis for the social insurance system reached €88,608 versus €20,147 for transplantation. Quite importantly, the mean transplantation cost includes a significantly higher cost in the first year, where it is comparable to that of hemodialysis [5]. This occurs because of the higher clinical requirements immediately post transplantation, such as systematic biopsies, immunosuppressive drug adaptation, and risk of acute rejection.

Despite guidelines provided by the French health authority (HAS), the Kidney Disease Improving Global Outcomes (KDIGO) and the European Renal Best Practice (ERBP), there are important disparities in the patient follow-up between transplantation centres. Numerous well-established clinical parameters are naturally taken into consideration for years for the follow-up adaptation, but novel scoring systems have also been developed to assist physicians and clinicians for the personalization of care.

Because of this, we were prompted to develop the Kidney Transplant Failure Score (KTFS). The KTFS is based on eight clinical and biological factors collected within the first year of transplantation, that are easily measurable and non–invasive [6]. The KTFS was associated with an area under the time-dependent ROC curve of 0.78 (CI95% = [0.71, 0.86]) for a prognostic up to eight years post-transplantation. Low-risk patients (KTFS ≤ 4.17) had a 93% probability of having a functional kidney at 8 years post-transplantation. In contrast, the graft survival of the high-risk patients (KTFS > 4.17) was estimated at 70%.

In the present study, we hypothesize that the efficiency of the kidney transplant recipient follow-up after one year post-transplantation could be further improved by adapting it to the risk of graft failure defined by the KTFS estimation. We propose video conferencing in addition to the KTFS estimation at one-year in order to 1) decrease the number of visits at hospital for low-risk patients without reduction in quality of life or graft survival and 2) increase the number of visits for high-risk patients with a possible improvement in graft survival.

The primary aim of the study is to evaluate the efficiency of a personalized follow-up for kidney transplant recipients that consists of adapting the frequencies of video conferencing at home and visits at hospital depending on the KTFS value. We expect such a personalized follow-up to be cost-effective compared to the conventional in-hospital follow-up strategy for both low- and high-risk patients groups.

## Methods

### Design

This is a phase IV, open label, randomized, multicentric and prospective study. Patients are allocated to one of two arms: the novel *eHealth program* versus the *standard of care* at hospital. The 1:1 randomization of patients is stratified on centers, and performed at 1-year post-transplantation. The participation for each patient is planned for 2 years. Figure 1 outlines the study design.

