### eHealth program (studied group)

Patients classified at low-risk (KTFS ≤ 4.17) will be interviewed three times by video conferencing (VC). The following medical parameters are collected before the VC using the USB device: pulse, weight, temperature, and blood pressures. Only 1 CC will be performed at hospital at each anniversary of the graft (with the same complete monitoring as outlined for the control group). In contrast, six visits at hospital (1 CC and 5 SV) will be scheduled for high-risk patients (KTFS > 4.17), with six additional interposed VCs to reinforce the follow-up.

Table 1 summarizes the schedule of visits at hospital and video conferencing according to the 1-year KTFS estimation.

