### Outcome measures

The primary outcome is composite and defined by the absence of major complications until two years post-randomization, i.e. a patient is alive with a functional kidney, without acute rejection episodes, without a decrease in the graft filtration rate (eGFR) higher than 25% estimated by the Levey’s formula [7] and without cancer. Other secondary outcomes will also be analyzed to evaluate the efficiency of the eHealth program: 1) The incremental cost-effectiveness ratios (ICER) comparing eHealth with at-hospital follow-up programs, estimated from the perspective of the health care system as the mean difference in two years costs divided by the mean difference in Quality-Adjusted Life Years (QALYs) calculated using the EuroQol EQ-5D questionnaire [8]. One ICER will be estimated for both the low and high risk patient groups. 2). The evolution of the transplant-specific or generic QoL respectively measured by the ReTransQoL and the SF36 questionnaires [9–11]. 3) The evolution of other psychological dimensions related to the stress by using the ways of coping checklist [12], the anxiety/depression by using the hospital anxiety and depression scale [13] and by using the post-traumatic growth inventory [14].

All outcomes will be compared between patients allocated to the eHealth program versus those in the control standard care group. Secondarily, the same comparisons will also be performed within each subgroup of graft failure susceptibility, i.e. KTFS +/- 4.17.

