Even if the randomized study we propose suffers from a small statistical power, the analysis will be based on a control group, i.e. comparable patients following standard of care. This design allows etiologic results without confounders, as requested by the Committee on Evaluating Clinical Applications of Telemedicine [22], in contrast to the majority of the literature in Telemedicine which is based on observational studies [23–25]. This may explain why the possible contribution of telemedicine in the improvement of medical follow-up is currently not clear [26, 27].

In conclusion, the current study allows to scientifically evaluate the etiologic impact of a novel eHealth program for the medical follow-up of kidney transplant recipients. We believe that the results will have an important impact in the transplantation community. Additionally, because the medical care of people with chronic disease is under the spotlight given the growing prevalence of such conditions in ageing populations, the proposed randomized design with 4 different sub-groups can be interesting to evaluate other personalized medicine programs.

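### Randomisation is stratified on centre but not on KTFS risk group, and the stated primary analysis does not adjust for it: avoidable chance imbalance with a modest loss of precision, not bias

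*Protocol article*

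**What the plan says.** The Design section names one stratification factor: "The 1:1 randomization of patients is stratified on centers, and performed at 1-year post-transplantation".

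Other sections give KTFS group a central role:

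- **Timing.** Background: "The KTFS is based on eight clinical and biological factors collected within the first year of transplantation". The score can therefore be known at the 1-year randomisation.
- **Prognosis.** Background reports graft survival at 8 years of 93% for low-risk and 70% for high-risk patients.
- **Intervention.** Under eHealth program and in Table 1, low-risk eHealth patients have video conferences in place of hospital visits. High-risk eHealth patients keep their hospital visits, "with six additional interposed VCs to reinforce the follow-up".
- **Hypotheses.** Background sets one aim for low-risk patients, "decrease the number of visits at hospital for low-risk patients without reduction in quality of life or graft survival", and another for high-risk patients, "increase the number of visits for high-risk patients with a possible improvement in graft survival".
- **Comparisons.** Outcome measures makes the pooled comparison the main one. It then adds that, secondarily, "the same comparisons will also be performed within each subgroup of graft failure susceptibility", and it plans cost-effectiveness ratios for the two risk groups.
- **Presentation.** The Discussion offers "the proposed randomized design with 4 different sub-groups" as a model for other programmes.

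Data analysis describes the primary analysis as a difference in percentages with a bootstrap 90% interval, compared with −3%. It lists risk classification as a covariate only for the psychological models.

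**The concern.** Nothing in the text keeps the arms 1:1 within each risk group, or keeps the share of high-risk patients equal between arms. This could matter in two places.

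- **Pooled primary comparison.** The arms may differ by chance in the strongest prognostic factor that the article reports. Neither the stated randomisation nor the stated primary analysis removes that difference, and the margin is only 3 points.
- **Within-group comparisons.** If the high-risk group is the smaller one, it may split unevenly. Precision would then be lost where the high-risk hypothesis and the high-risk cost-effectiveness ratio are examined.

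The question is how large either effect is.

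**Working it through.** **Inputs from the article.** Sample size: 125 per arm, 90% free of complications in both arms, 3-point margin, one-sided 5% level, power 20%, 1,237 per group for 80% power. Background: 93% and 70% graft survival at 8 years.

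**Assumptions.** The high-risk share is not given, so I take 10% to 50%. The gap between risk groups on the 2-year composite is not given either, so I take 10, 16 and 23 points. The last is the 8-year gap (93 − 70); it concerns a different endpoint and horizon and serves as an upper end.

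**Step 1: reproduce the stated figures.**
- SE of the difference = √(2 × 0.9 × 0.1 / 125) = 0.0379, or 3.8 points.
- Power = Φ(0.03/0.0379 − 1.645) = 19.6%, against 20% stated.
- n per group for 80% power = 2 × 0.09 × (1.645 + 0.842)² / 0.03² = 1,237, as stated.

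**Step 2: split of the high-risk patients.** With 250 patients, arms of 125 and no control of KTFS, the number of the H high-risk patients in one arm is hypergeometric. Centre stratification is ignored here.

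| Assumed share | H | 95% range in one arm | Chance of 60:40 or worse |
|---|---|---|---|
| 10% | 25 | 8 to 17 | 40% |
| 20% | 50 | 19 to 31 | 15% |
| 25% | 62 | not computed | 6% |
| 30% | 75 | 30 to 45 | 5% |
| 40% | 100 | 42 to 58 | 1.4% |
| 50% | 125 | 55 to 70 | 0.2% |

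At 25% the result depends on rounding: 5.6% with 62 high-risk patients, 8.0% with 63. In the low-risk group the chance is about 0.2% or less throughout.

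**Step 3: cost of an uneven split.** Efficiency relative to an even split is 4f(1 − f), where f is the fraction in one arm. At f = 0.6 this is 4 × 0.6 × 0.4 = 0.96: a loss of 4%, or a standard error about 2% larger (1/√0.96 = 1.02). The average loss in the high-risk group is about 4% at a 10% share and below 2% from a 20% share upward.

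**Step 4: effect on the pooled difference.** The SD of the between-arm difference in high-risk share is about √(2q(1 − q)/125). At q = 0.25 this is √(2 × 0.25 × 0.75/125) = 0.055, or 5.5 points. Multiplying by the gap gives the SD that imbalance adds to the pooled difference. Power without it uses √(3.79² − SD²) as the standard error.

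| Assumed gap | SD added | Shift at 1.96 SD | Share of variance | Power if removed |
|---|---|---|---|---|
| 10 points | 0.5 | 1.1 | 2% | 19.9% |
| 16 points | 0.9 | 1.7 | 5% | 20.3% |
| 23 points | 1.3 | 2.5 | 11% | 21.0% |

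From 19.6%, the gain in power is 0.2 to 1.3 points.

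**Step 5: after the change.** Three centres × two risk groups = 6 strata, or 250/6 ≈ 42 patients each on average. With permuted blocks of 4 (an assumption), imbalance is at most 2 patients per stratum, so at most 6 per risk group across centres. This bound applies to newly randomised patients. The sample size does not change.

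**The case against.** Stratifying on centre alone is an accepted choice. KTFS is a baseline variable, so the randomised comparison stays valid within each risk group. The unadjusted interval already covers this chance variation on average. The within-group comparisons are secondary and would stay weak with perfect balance: on the article's own 90% and 3-point inputs, non-inferiority power is about 8% to 14% in high-risk and 14% to 19% in low-risk patients. Covariate adjustment is often left to an analysis plan that is not shown here. All of this stands, and it limits the point to precision.

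A reader might infer that the comparisons are biased, or that a badly lopsided high-risk group is likely. The documents support neither. Treating each high-risk patient as an independent coin toss and counting 25:37 as a 60:40 split gives about 16% for 62 patients. But 25 of 62 is 40.3%, short of that split, and the arms are fixed near 125 each; the figure is about 6%. Nor is a 1.96 SD shift of up to 2.5 points an error to set alone against the 3-point margin: it is one part of an overall standard error of 3.8 points.

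Figure 1 is not available here. Its legend speaks of allocating patients into one of four sub-groups, which could mean randomisation within KTFS group. That possibility stands, so it cannot be said with high confidence that the trial omits this stratification, only that the Design text does.

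What does not fall away is that the text names its stratification factor, and a later analysis plan can adjust for KTFS but cannot change allocations already made.

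**Conclusion.** The point holds in a limited form. As written, the allocation leaves to chance the factor that sets the intervention and organises the hypotheses and subgroup comparisons, and the stated primary analysis does not recover the loss. An uneven high-risk split is fairly likely only if that group is small, and even then the cost in efficiency is modest. For the pooled result, imbalance accounts for about 2% to 11% of the variance at a 25% share.

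These sizes rest on the assumed high-risk share and risk-group gap, and the conclusion on the Design text being complete. The change is worth making because it is cheap and the trial has little power to spare. It will not remedy the low power.

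**What to change.** 1. **Confirm the allocation.** Check Figure 1 and the full protocol. If patients are already randomised within KTFS group, correct the Design section to say so and analyse accordingly.
2. **If not, stratify from now on.** For patients not yet randomised, stratify by centre and KTFS group (≤ 4.17, > 4.17), giving 6 strata. The Schedule section reports 38 patients included, all at Nantes. Their allocations stay, and about 250 − 38 = 212 patients could still benefit.
3. **In any case, use both factors in the analysis.** Estimate the primary difference stratified by or adjusted for KTFS group and centre, for example by bootstrapping within strata with a standardised risk difference. This recovers most of the precision even if the lists cannot be changed.

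The cost is a small update to the randomisation lists or system, ideally before the other centres start, and a small addition to the analysis. Six strata for 250 patients is not over-stratified.

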**Figure 1 Fig1:**
[figure not shown]
**Summary of the TELEGRAFT study design.** Circles represent the allocation process for patients into one of the four sub-groups.

#### Participants

Initial inclusion criteria were: 1) patients were alive with a functional kidney at one-year post-transplantation, 2) patients with high-speed internet access, usually digital subscriber line or fiber optic cable, 3) patients without ongoing CMV or BKV infection, 4) men or non-pregnant women, 5) patients without mental disorders and 6) patients with a written informed consent. Participants will be recruited from the University hospitals in Nantes, Paris (Necker) and Lyon (Edouard Herriot). All of these transplantation centers participate to the DIVAT and the CENTAURE networks (http://www.divat.fr, http://www.fondation-centaure.org). The recruitment will be performed at the 1-year post-transplantation hospital visit.

### Video conferencing devices

When patients are allocated in the *eHealth program*, they receive two devices: 1) A USB flash drive which allows the collection of medical information before the video conferencing. The plug-in of this device opens up a secure connection to the web via an intuitive interface specially designed for non-internet specialist patients. This hardware contains a security token for an easy and secure authentication. No software installation is necessary, only an internet connection is required, and provides web-browser independent access. 2) A tablet computer (iPad®, Apple Inc) specifically devoted for the video conferencing. Similar security is ensured by a system comparable to the USB device (token principle). Of note, the use of personal computers was first tested for 12 patients, but was concluded to be too difficult to apply in practice for several technical reasons. These included the requirement for software installation, variability in computer devices, operating systems and firewalls. Because kidney transplant recipients constitute an ageing population, we endeavored to make access as simple as possible.

### Standard care (control group)

Patients classified at low-risk of graft failure within the first 8 years post-transplantation (KTFS ≤ 4.17), will be scheduled 4 visits at hospital per year, whilst high-risk patients (KTFS > 4.17) will visit hospital 6 times. These Standard Visits (SV) consist of clinical examinations (weight and blood pressure measurements) with standard blood and urine monitoring (network file system, blood electrolytes, uremia, creatinemia and trough levels of immunosuppressive drugs). Among the 4 or 6 visits (depending of the risk group), 1 visit is devoted to a Complete Check-up (CC): detailed medical examination, additional pathology parameters (daily proteinuria, albuminemia, 25(OH)vitamin D, parathyroïd hormone, bilirubinemia, serum glutamic oxaloacetic transaminase, serum glutamic-pyruvic transaminase, Gamma-glutamyl transferase, phosphatase alkalinity, prostate specific antigen, viral serologies (Hepatitis B, Hepatitis C, HIV, CMV, EBV) and anti HLA responses screened by Luminex technology), morphologic exams (ultrasound scan and doppler sonographic of the graft artery and pulmonary X ray), and questionnaires related to quality of life (QoL) and psychological dimensions.

### eHealth program (studied group)

Patients classified at low-risk (KTFS ≤ 4.17) will be interviewed three times by video conferencing (VC). The following medical parameters are collected before the VC using the USB device: pulse, weight, temperature, and blood pressures. Only 1 CC will be performed at hospital at each anniversary of the graft (with the same complete monitoring as outlined for the control group). In contrast, six visits at hospital (1 CC and 5 SV) will be scheduled for high-risk patients (KTFS > 4.17), with six additional interposed VCs to reinforce the follow-up.

Table 1 summarizes the schedule of visits at hospital and video conferencing according to the 1-year KTFS estimation.

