**Table 1 Tab1:** **Schedule of the four subgroups in the TELEGRAFT study**

	High-risk (KTFS > 4.17)		Low-risk (KTFS ≤ 4.17)	
	Standard	eHealth	Standard	eHealth
Day 0 (inclusion)	CC and data collection (written consent, QoL)			
Week 03	-	VC	-	-
Week 06	SV	SV	-	-
Week 09 (Month 2)	-	VC	SV	VC
Week 12 (Month 3)	SV	SV	-	-
Week 15	-	VC	-	-
Week 18 (Month 4)	SV	SV	SV	VC
Week 21	-	VC	-	-
Week 24 (Month 6)	SV	SV	SV	VC
Week 27	-	VC	-	-
Week 30	SV	SV	-	-
Week 33	-	VC	-	-
Week 36	SV	SV	-	-
Week 39	-	VC	-	-
Week 42	SV	SV	-	-
Week 45	-	VC	-	-
Week 48	SV	SV	-	-
Week 50	-	VC	-	-
Week 52 (Month 12)	CC and data collection (pathology, QoL, morphologic exams)			
Month 13	-	VC	-	-
Month 14	SV	SV	-	-
Month 15	-	VC	SV	VC
Month 16	SV	SV	-	-
Month 17	-	VC	-	-
Month 18	SV	SV	SV	VC
Month 19	-	VC	-	-
Month 20	SV	SV	-	-
Month 21	-	VC	SV	VC
Month 22	SV	SV	-	-
Month 23	-	VC	-	-
Month 24	CC and data collection (laboratory works, QoL, morphologic screaming)			

SV, Standard Visit at hospital; CC, Complete Check-up at hospital; VC, Video Conferencing at home; Qol, Quality of Life.

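### Low-risk standard patients have scheduled bloods at 8 post-baseline visits and low-risk eHealth patients at 2, while the eGFR and rejection components are not tied to visits common to both arms, which favours non-inferiority

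*Protocol article*

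**What the plan says.** Under Outcome measures, the primary outcome is "defined by the absence of major complications until two years post-randomization". Besides survival with a working graft and no cancer, a patient must be "without acute rejection episodes, without a decrease in the graft filtration rate (eGFR) higher than 25" per cent. The article states no assessment visit for the eGFR component and no confirmation rule.

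Under Standard care, low-risk patients "will be scheduled 4 visits at hospital per year", and each standard visit (SV) comes "with standard blood and urine monitoring (network file system, blood electrolytes, uremia, creatinemia and trough levels of immunosuppressive drugs". One visit a year is the complete check-up (CC).

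Under eHealth program, the low-risk patient has three video conferences (VC) a year. For these the article states: "The following medical parameters are collected before the VC using the USB device: pulse, weight, temperature, and blood pressures". No blood test is listed. For hospital attendance: "Only 1 CC will be performed at hospital at each anniversary of the graft", with the same monitoring at that check-up as in the control group.

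Table 1 sets an SV for standard care against a VC for eHealth at all six interim low-risk time points. Under Data analysis, eHealth is declared non-inferior if the lower limit of the 90% confidence interval for the difference in complication-free patients lies above −3%. The trial is open label.

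**The concern.** Two components of the composite depend on someone looking. An eGFR fall is seen only when creatinine is measured, and a subclinical rejection is usually pursued because a blood result prompted it. If any creatinine value in the two years can make a patient a failure, the arm with more values records more failures, even when the grafts behave identically. In low-risk patients that arm is standard care.

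The complication-free percentage under eHealth then looks better than it is. In a non-inferiority test this error runs towards the claim. Randomization does not remove it, because the difference in looking is part of the allocated programme. The protocol also plans the comparison within each risk group. In the low-risk comparison nothing dilutes the effect; in the pooled test the high-risk patients do.

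**Working it through.** **1. The plan's own figures.** With 90% complication-free in both arms, a margin of 0.03 and one-sided α of 0.05, n = 2 × 0.09 × (1.645 + 0.842)² / 0.03² ≈ 1,236.5, so 1,237 per arm, as stated. With 125 per arm, SE = √(2 × 0.09 / 125) = 0.0379 and power = Φ(0.03/0.0379 − 1.645) = 0.196, against the stated 20%. Both reproduce.

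**2. Scheduled blood monitoring after Day 0, from Table 1.**
- Low-risk standard: SV at weeks 9, 18 and 24 and months 15, 18 and 21, plus CC at week 52 and month 24 = 8.
- Low-risk eHealth: CC at week 52 and month 24 = 2.
- High-risk: 13 SV + 2 CC = 15 in each arm. The text gives six hospital visits a year where Table 1 shows eight SV and a CC in year 1. Those places need reconciling, but the arms are equal under either.

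**3. Chance of at least one recorded fall above 25%.** None of these inputs is in the documents; all are assumptions. Two-year change in log eGFR has mean −3% and SD 10% and is linear in time. Error is log-normal at baseline and at each visit. One value below 75% of baseline is an event.

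| Within-patient CV | 8 looks | 2 looks | Artefact A (points) | Month 24 only, either arm |
|---|---|---|---|---|
| 5% | 2.5% | 1.8% | 0.7 | 1.8% |
| 7% | 6.3% | 3.7% | 2.6 | 3.4% |
| 8% | 9.5% | 5.2% | 4.3 | 4.4% |

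The last column is the same for both arms, so judging eGFR at month 24 alone removes the differential.

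**4. Effect on the pooled test.** Place the true difference at the margin (90% against 87%). SE = √(0.90 × 0.10/125 + 0.87 × 0.13/125) = 0.0403. With low-risk share f, the observed difference moves by f × A, so P(declare non-inferiority) = Φ(f × A / 0.0403 − 1.645), with a normal approximation standing in for the bootstrap.

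| CV | f = 50% | f = 75% |
|---|---|---|
| 5% | about 6% | about 6% |
| 7% | about 9% | about 12% |
| 8% | about 13% | about 20% |

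Nominal is 5%. Adding A in full slightly overstates the shift, because some of these patients would already have failed on another component.

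**5. Check without an eGFR model.** At the margin the true eHealth event rate is 13%. If 10% or 20% of all eHealth events went unrecorded, the observed rate would rise by 1.3 or 2.6 points and the error would be 9.4% or 16.7%. If only half of the events are in low-risk patients and the same shares of those are missed, it is 6.9% or 9.4%.

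**6. Upper limit on plausibility.** The Sample size section allows 10% events for the whole composite. At CV 8%, 75% low-risk patients would contribute 0.75 × 9.5 = 7.1 points from eGFR alone in the standard arm, which is already near the edge. At CV 10% the 8-look figure is about 17.7%, and 0.75 × 17.7 = 13.3 points exceeds the total.

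**The case against.** The strongest reply is that the article never says any eGFR fall counts at any visit. The two-year phrase qualifies the absence of complications as a whole, and Table 1 marks data collection only at Day 0, week 52 and month 24, which all four subgroups share. If eGFR is judged only there, the eGFR artefact largely vanishes. That reading is possible, but the text does not state it, and the wording more naturally covers the whole window. The subclinical rejection part remains under either reading.

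The size also depends on the event rule. If two consecutive low values were required in the 8-visit arm, its figures would fall to about 1.4% at CV 7% and 2.2% at CV 8%, so most of the artefact comes from counting single unconfirmed values. This stands, and is why the result is given as conditional.

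Other points also stand in part. Sustained eGFR loss, graft loss and death are still picked up in both arms. High-risk eHealth patients have extra video conferences with equal bloods, which could prompt some additional work-ups against eHealth. Late treatment of missed rejection could worsen true outcomes under eHealth; that is a treatment effect and does not cancel differential detection. If outside-laboratory bloods accompany the VCs, the count changes, but the article does not describe any.

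The admitted 20% power makes a positive result unlikely. It does not make one easier to interpret if it occurs.

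**Conclusion.** The visit counts are firm: 8 against 2 in low-risk patients, equal in high-risk patients. On the natural reading of the outcome, the low-risk comparison is tilted towards non-inferiority, and the pooled test is tilted by a diluted amount.

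The size is not derivable from the documents, since the low-risk share, component rates and eGFR variability are not given. For a CV of 5–8%, single unconfirmed values and 50–75% low-risk patients, the artefact is about 0.7–4.3 points in low-risk patients and the one-sided error at the margin is about 6–20%. The rejection part has no figure.

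A reader might infer that a large bias is certain, for instance an error near 50% by taking CV 10% and 75% low-risk. The documents do not support this: that case breaks the protocol's own 10% event rate, and the article does not settle at which visits eGFR is judged.

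**What to change.** Define the eGFR component in both arms from the common check-ups only: the month-24 CC value against the Day-0 CC value. Graft loss and death already count as events, so no substitute value is needed for them. State that interim SV creatinine is not used for the endpoint.

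Keep acute rejection in the primary composite, because it is a key possible harm of reduced surveillance. Pre-specify a sensitivity analysis of the composite without it, reported alongside the primary result, because its detection depends on visit frequency. If blood tests are in fact done around the VCs, say so.

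The cost is wording and one added analysis; the check-up values are already collected in both arms, and no visit changes. The drawback is that eGFR falls that recover before month 24 no longer count, so there will be slightly fewer events.
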